#### Data retention and archiving

Once the research project is completed, all study data will be stored and secured for the length of time required by the award (minimum 3 years) with additional extension as deemed needed by the study Co-PIs, based on ongoing secondary analyses of the data. At this juncture, data will be removed from the NU EDW and secured with password-protected and user-access restricted research data drives/servers at NU. As per National Institutes of Health requirements, a research dataset will be created that is stripped of all patient health information and personally identifiable information for more public, generalized use.

#### Oversight and monitoring

A Data Safety and Monitoring Board (DSMB) will ensure the safety of subjects and the validity and credibility of the trial. This board will include an experienced pediatric gastroenterologist, a pediatric surgeon, and a patient or parent of a patient who underwent GI surgery. All board members are not involved in the study and are free of competing interests. Interim analyses will be conducted every 7 months and include any potential adverse events (event rates), timing and completeness of data collection, adequacy of sample size, comparability of treatment clusters [35]. The DSMB can ask for more frequent reporting if concerns arise. Approximately 2 weeks before the DSMB meeting, the study statistician will send a report to the DSMB members that includes patient recruitment, ratio of consent to randomization, attrition, and any adverse events by treatment, labeled A or B. While the study is not blinded by design, the data will be presented in a blinded fashion to reduce any bias associated with knowing the intervention cohort. The board will review the results and assure that the conduct of the trial is acceptable. Any recommendations of the committee will be directly made to the Co-Principle Investigators. The trial will be stopped if the committee identifies any significant safety concern which warrants stopping the trial.

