### Randomization and timeline

The 18 participating sites will be randomly assigned by the study statistician to one of three clusters for the stepped-wedge design, with each cluster consisting of six sites, in turn, being randomly assigned to an intervention start period [32–34]. Given that many sites have already initiated some ERP elements, a study design that randomizes sites or patients to a control arm without any ERP elements is no longer feasible [33, 34]. Figure 4 shows the study design. All sites will initially have at least a 6-month “control” phase during which baseline, pre-intervention data will be collected. Then, each cluster will have a 12-month ENRICH-US implementation or “intervention” phase. Post-intervention data will be collected during a “sustainability” phase of at least 1 year and, for up to 2 years at some sites. Each cluster will be a LC to collectively share and learn from each other about contextual adaptations and implementation strategies, guided by the five AIFs. Figure 5 shows the time schedule of enrollment for subjects.

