### Study phases

#### Installation phase

Training for the “control phase” data collection of the site PI, research coordinator, and data abstractors will take place during the first two quarters of year 1. Training will focus on the creation of site-specific workflows for patient recruitment, enrollment criteria, consent processes, and the use of data abstraction tools. Given the stepped-wedge design, each site PI and research coordinator will also recruit and create a site implementation team, 6–9 months prior to the cluster’s intervention start period, to optimize team engagement. For example, each cluster will establish their teams in 6-month intervals (e.g., cluster 1 in the second quarter of year 1; cluster 2 in the final quarter of year 1; and cluster 3 in the second quarter of year 2). Each site implementation team will include, in addition to the site PI and study coordinator, at least one anesthesia champion, one patient advocate liaison, and one hospital-level QI leader.

Similarly, a monthly video-conference LC meeting with each cluster will begin about 1 month after each site in the cluster has created their implementation team. The LC approach includes sharing of obstacles and barriers to implementation of specific elements, reporting on the use of implementation toolkit contents (e.g., order sets, patient education materials) to assist with implementation, providing updates about rapid cycle small tests of change with data feedback, and learning about and sharing strategies to overcome barriers to implementation. All LC video-conference sessions will be audio-video recorded and serve as a source of data that will be analyzed qualitatively to provide a catalog of the multiple contextual adaptations and strategies undertaken by sites to optimize adaptation and implementation.

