#### Control phase

This phase encompasses the AIF installation phase. All clusters begin the control phase at the same time but continue for varying periods (6–18 months). Each site coordinator will recruit, screen, enroll, and consent eligible patients. This phase consists primarily of individual-level patient data collection. Patients and parents will complete web-based HRQoL assessments preoperatively, at 2–5 days, and at 4–6 weeks, post-operatively. This phase involves abstraction of existing EHR data by the site coordinator about current, standard perioperative care received by patients. Site-specific barriers and facilitators to implementation will be assessed by semi-structured, telephone interviews, conducted with each site’s PI and coordinator.

During the control phase, standard perioperative surgical care will be provided. Some elements of the ENRICH-US intervention may already be standard of care and, during the control phase, these elements will continue to be offered and details about the use of these elements will be collected.

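### The A/B labels on DSMB adverse-event tables cannot mask treatment in this stepped wedge, and a split by treatment alone is confounded by calendar time

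*Protocol article*

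**What the plan says.** Under Oversight and monitoring, the protocol article sets the review interval ("Interim analyses will be conducted every 7 months") and lists the contents of the statistician's report, which include "any adverse events by treatment, labeled A or B". It concedes that the study itself is open, but adds that "the data will be presented in a blinded fashion to reduce any bias associated with knowing the intervention cohort". The board's judgement has a direct consequence: "The trial will be stopped if the committee identifies any significant safety concern which warrants stopping the trial".

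The schedule is set elsewhere. Control phase: "All clusters begin the control phase at the same time but continue for varying periods", from 6 to 18 months. Randomization and timeline: three clusters, "with each cluster consisting of six sites", then a 12-month implementation phase and one to two years of sustainability. Installation phase: "each cluster will establish their teams in 6-month intervals". Trial status: 3.5 years of recruitment.

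The section on statistical analysis of Aim 1 recognises that calendar time may be related both to exposure and to outcome, and brings it into every analysis as a potential confounder. Oversight and monitoring does not say whether that extends to the DSMB tables.

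**The concern.** Crossover is one-way. No intervention patient accrues before month 6 and no control patient after month 18. This has two consequences for a table with columns A and B.

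First, the size of each column shows which one is the intervention, so the stated protection against bias is not delivered.

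Second, the columns represent different stretches of calendar time. If complication rates move for reasons unrelated to the intervention, A and B will differ with no treatment effect. A downward trend could hide harm and an upward one could raise a false alarm. The article gives some reason to expect change over time, since it notes that many sites have already begun some elements of the protocol. This is the only between-treatment safety display that the article describes, and it informs the decision whether to stop the trial.

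**Working it through.** **Inputs from the article.** Three clusters of six sites; control phases of 6 to 18 months from a common start; team formation at 6-month intervals; 12 months of implementation; 12 to 24 months of sustainability; 42 months of recruitment; reports every 7 months; background complication rates of 20 to 40%.

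**Assumptions.** Crossovers at months 6, 12 and 18 (the middle one inferred from the 6-month spacing); equal accrual across sites and months; reports timed from the common start; implementation and sustainability both counted as intervention; linear drift of 1, 3 or 5 percentage points a year, in either direction. The article gives no drift figure.

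**Timeline check.** 6 + 12 + 24 = 12 + 12 + 18 = 18 + 12 + 12 = 42 months, which reproduces the stated 3.5 years.

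**Site-months at report month t.** Control = 6 × Σ min(t, x) over x = 6, 12, 18. Intervention = 18t − control. At month 7, control = 6 × (6 + 7 + 7) = 120 and intervention = 126 − 120 = 6. At month 42, control = 6 × (6 + 12 + 18) = 216 and intervention = 756 − 216 = 540.

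**Mean calendar month per label.** Control = Σ[min(t, x)²/2] / Σ min(t, x). Intervention = Σ[(t² − x²)/2] / Σ(t − x), over clusters already crossed. At month 42, control = 252/36 = 7.0, intervention = 2394/90 = 26.6, gap = 19.6 months.

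**Spurious difference with no treatment effect** = drift per year × gap/12. At month 42 and 1 point a year, 19.6/12 = 1.6 points.

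| Report month | Control site-months | Intervention site-months | Mean month, control | Mean month, intervention | Gap (months) | Spurious difference at 1 / 3 / 5 points a year |
|---|---|---|---|---|---|---|
| 7 | 120 | 6 | 3.35 | 6.50 | 3.15 | 0.3 / 0.8 / 1.3 |
| 14 | 192 | 60 | 5.88 | 10.60 | 4.72 | 0.4 / 1.2 / 2.0 |
| 21 | 216 | 162 | 7.00 | 15.17 | 8.17 | 0.7 / 2.0 / 3.4 |
| 28 | 216 | 288 | 7.00 | 19.25 | 12.25 | 1.0 / 3.1 / 5.1 |
| 35 | 216 | 414 | 7.00 | 22.98 | 15.98 | 1.3 / 4.0 / 6.7 |
| 42 | 216 | 540 | 7.00 | 26.60 | 19.60 | 1.6 / 4.9 / 8.2 |

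**Masking.** Applying the 60% enrollment rate to the annual volume (an assumption) gives 0.6 × 616/18 = 20.5 patients per site per year. The first report then holds about 120 × 20.5/12 = 205 control patients and 6 × 20.5/12 = 10 intervention patients. Even without denominators, event counts would give the label away: at 20 to 40%, about 41 to 82 events against 2 to 4. From month 28 one column gains no patients between reports, while the other gains 126 site-months each time.

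**Overlap.** In months 6–18, control contributes 6 × (0 + 6 + 12) = 108 site-months and intervention 6 × (12 + 6 + 0) = 108. That is 108/216 = 50% of all control time and 108/540 = 20% of all intervention time.

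**The case against.** The strongest reply is that the article does not say the tables are cumulative, unstratified or unadjusted. Pooling is read from the phrase about treatment. A DSMB charter or the full protocol, neither shown, could add tables by period, and the Aim 1 section already commits to handling calendar time. This stands as a limit: the confounding half is conditional on the display being what the sentence describes. It does not rescue the masking half, because period tables would make the labels more obvious.

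Second, the drift is assumed, and its effect is largest at month 42, when recruitment ends and little is left to stop. That is fair. At months 7 and 14 the spurious difference is 2 points or less across the range used, small beside background rates of 20 to 40%. No statistical boundary is set, so a shift of that size would not by itself trigger a decision.

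Third, the study is openly unblinded and the article claims only to reduce bias, so an unmasked board does limited harm. That also stands. The fault is a stated safeguard that does not work, not damage to the trial.

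A reader might infer that the labels share no calendar time, that the plan ignores secular trend altogether, or that a particular harm would be hidden. The documents support none of these: there is a 12-month overlap, calendar time is named as a confounder, and no trend in complications is given.

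**Conclusion.** The point holds in two parts of different strength.

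The masking claim fails on the article's own schedule. No drift assumption is needed, only that the board knows the design and sees counts or denominators by label. Unequal site volumes (5 to 120 patients a year) would change the figures but not the pattern.

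The confounding holds if events are shown by treatment alone, which is the natural reading. Its size is modest early and grows with follow-up: about 0.7 to 3.4 points at month 21 and 1.6 to 8.2 at month 42 for an assumed drift of 1 to 5 points a year, in either direction. The primary length-of-stay analysis is not affected. The change is worth making because the display informs a stopping judgement and the repair is cheap.

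**What to change.** In each DSMB report, tabulate adverse-event rates by calendar half-year, cluster and phase (control, implementation, sustainability). Add a rate difference adjusted for calendar period and hospital. State beside it that it rests on concurrent controls only in months 6–18 and on modelling afterwards. The change reduces the confounding but cannot remove it, because 540 − 108 = 432 intervention site-months have no concurrent control.

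Replace the blinding sentence with a statement that the board is effectively unmasked. If a charter already provides tables by period, a cross-reference to it would settle the confounding half.

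Cost: a few more tables in an existing report, small cells in the early periods, and no formal masking of the board.

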## Discussion

This study protocol will allow for the evaluation of the effectiveness, implementation, and sustainability of all the recommended elements of the ENRICH-US intervention. Prior pediatric surgery studies have typically involved ≤ 6 ERP elements, while most adult ERPs have more than 20 elements. The study has been designed and powered to detect a decrease in LOS between cases (receipt of ENRICH-US intervention) and controls (receipt of standard post-operative care). Improvements in a wide variety of secondary outcomes, such as opioids use, post-operative complications, and patient/family HRQoL may also occur. Regardless of the effectiveness, this study will reveal important information about the uptake and sustainability of a complex intervention at a wide range of pediatric surgical centers. This information will be highly informative for future, large-scale QI efforts in pediatric surgery. Tangible outputs include the creation of implementation toolkits and coaching videos. These efforts align with the shift in national health policy from a focus on quantity to a focus on quality and value-based care. The patient-reported outcomes provide useful insight to the specific aspects of care most highly valued and prioritized by patients and families. In addition, prior pediatric studies have had limited acknowledgement of bias, inconsistent outcomes, and lacked adequate controls.

While the success of this study has far-reaching implications for advancing pediatric surgical care and improving outcomes for pediatric patients undergoing GI surgery, next steps include expansion and examination of a similar ERP for younger patients, for broader populations including critical care and care of medically complex pediatric populations, and for a wider-spectrum of pediatric surgical procedures.

### Trial status

This study can be found on ClinicalTrials.gov under the registration number NCT04060303. The current protocol Version 2.0 20-Jul-2020. Enrollment began July 2020, and recruitment will continue for 3.5 years.

## Data Availability

The study team plans to write up study results for publication in scientific journal articles to reach healthcare professionals. Dissemination of the results of the study is an essential part of the proposed activities and the dissemination plan includes multiple approaches. The investigators wish to make the results available both to the community of clinicians who care for IBD GI patients and to the patients and families with IBD. A key goal of the dissemination plan will be to prepare appropriate materials, as soon as data are valid and reliable. Study results will also be posted on ClincialTrials.gov. All data collected during the study will be made available in a de-identified manner. In addition to the peer-reviewed publication of study results and the dissemination of findings through publicly available websites, blogs, and newsletters, the PI and Biostatistics Director will create a patient de-identified data set that will be made publicly available to researchers. These public files will include clinical data and outcomes collected through REDCap for the complete study, as well as raw data for the HRQoL surveys. All data will be fully de-identified at the patient- and hospital-level. Data requests will be made to the PI (via direct email contact or through the study website) who will arrange for secure transfer of data through a secure web-based data sharing tool (such as Dropbox). A copy of the study protocol, data definition dictionary, and public use file with instructions will also be generated for ease of use. Data will be made available in a format that will easily be used in mainstream software analysis packages (e.g., ASCII, SAS). The data will be made available as soon as possible but no later than 1 year of the completion of the funded study period for the parent award or upon acceptance of the data for publication, whichever is earlier. All individually identifiable health information will be stripped from the public use data sets, as per Health Insurance Portability and Accountability Act (HIPAA) guidelines, as well as, the omission of indirect identifiers that are not listed as patient health information but could lead to “deductive disclosure” such as comment fields and study site numbers. Furthermore, participating sites will be protected by stripping all actual names and creating a random number to represent data collected from each site.

## Abbreviations

ACS NSQIP: American College of Surgeons National Surgical Quality Improvement Program
AIFs: Active Implementation Frameworks
APSA: American Pediatric Surgical Association
CD: Crohn’s disease
CFR: Code of Federal Regulations
DCC: Data Coordinating Center
EDW: Enterprise Data Warehouse
EHRs: Electronic health records
ENRICH-US: ENhanced Recovery In CHildren Undergoing Surgery
ERAS: Enhanced recovery after surgery
ERPs: Enhanced recovery protocols
GI: Gastrointestinal
IBD: Inflammatory bowel disease
HRQoL: Health-related quality of life
LC: Learning Collaborative
LOS: Length of stay
NGT: Nasogastric tube
NU: Northwestern University
PDF: Portable Document Format
RECOvER: Enhanced Recovery Compliance, Outcomes, and Elements Research
REDCap: Research Electronic Data Capture
PedSRC: Pediatric Surgery Research Collaborative
QC: Quality control
QCA: Qualitative comparative analysis
UC: Ulcerative colitis
VTE: Venous thromboembolis
